During a second visit, one month after initial LLIN distribution the correct usage of LLINs will be evaluated: the correct hanging of LLINs will be confirmed and household members will be asked to explain how they use the net. If needed, instructions about correct use will be repeated and additional nets can be provided if nets are missing or found to be torn. A third visit will occur to re-assess the quality and use of the nets 6 months after the first visit, in conjunction with the second round of IRS. At this point new ownership and quality will be re-assessed and new nets will be distributed as needed. All information on net use and quality will be recorded (appendix D).

*Focal Screening and Treatment (FSAT)*

Screening of a sentinel population within households

The FSAT utilizes individuals aged 6 month to 20 years as a sentinel group to indicate malaria exposure in the household because this age-group experiences the highest parasite burden [23-24]. For this age group all individuals will be tested for parasites using RDTs regardless of presence of symptoms or not. However clinical care will not be restricted to just this age group. All age groups may experience clinical malaria in our setting ([name] *et al.*, in preparation) and therefore those individuals over 20 years who are found to have fever will also be tested by RDT and receive treatment as oart of the FSAT intervention.

The FSAT campaign will take place in intervention hotspots in March 2012; a second round of FSAT is planned to take place in September 2012. Both campaigns will follow identical procedures.

Screening the sentinel group

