Blood samples will be collected from all individuals aged between 6 months and 20 years. Blood will be collected by fingerprick and used to test for malaria by rapid diagnostic test (Premier Medical First Response Combo^®^,HRP-2 & LDH based), for determination of haemoglobin levels using a Copack Colour Scale ® (Oststeinbek, Germany), to prepare a microscopy slide and to collect blood into an EDTA microtainer tube and onto a filter paper. RDTs will be used for clinical decision-making; slides will read after the campaign to determine the relative sensitivity of RDTs and PCR in the study setting. The Copack Haemoglobin Colour Scale system has been available since 2001 and is a reliable and validated method to assess haemoglobin levels. The test consists of a drop of blood being placed on the test strip, and after 30 seconds is compared to the hue on the provided colour scale. The gradient of the colour scale indicates whether and how severely anaemic a person is with the scale ranging from <4 to 14 g/dl of haemoglobin. The collected blood samples will be analysed for parasite prevalence by microscopy PCR and the detection of malaria-specific antibody responses by ELISA (see section g: laboratory analyses).

Screening the non-sentinel group

In addition to testing the sentinel age-group, all other individuals aged above 20 years will have their temperature by ear thermometer and blood samples taken by fingerprick. Those that are febrile (as defined by the range of the specific thermometer used) will be tested for malaria using RDTs otherwise blood will be collected as described above for the same purposes.

Using the sentinel population to detect microscopic and submicroscopic parasite carriers

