Treatment will be carried out using artemether-lumefantrine (Coartem, AL) according to national guidelines. AL is an antimalarial drug with an excellent safety profile; limited data on safety are available for children under 6 months and pregnant women, both groups will therefore be excluded from AL treatment (see below) but receive clinical care when necessary. As detailed below, all those who are given Coartem will be actively followed-up to monitor any side effects. This monitoring will happen on all days of treatment and one week after the start of treatment. If given to parasite-free individuals, AL will provide an effective prophylactic effect for 3-4 weeks, which has been shown to be highly beneficial for malaria control purposes in high endemic regions [36]. In parasite carriers, AL effectively clears asexual parasites and gametocytes, the parasite stage responsible for transmission [35]; the timing of FSAT is chosen to ensure individuals are parasite and gametocyte-free before the start of the peak transmission season. For those receiving AL, the first dose will be supervised and then instructions will be provided for taking of the second dose which will be issued. Teams will return to compounds the next day to administer and supervise the third dose and distribute the fourth. They will return again on the third treatment day to again administer and supervise the fifth dose and distribute the sixth. At the same time any side effects will be noted. (see appendix G & H).

All participants will be told their haemoglobin level immediately, and any person found to be anaemic will be provided haematinics according to national guidelines.

Treatment of risk groups: children <6 months and pregnant women

Children below 6 months of age will be excluded from the study; they will be screened for fever and referred to a health facility where needed but will not be included in FSAT.

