**Appendix G: Adverse reporting monitoring form for FSAT**

Call up each participant treated, **one by one**.

Area (Cell)_____________

Compound/house code_______________

Participant’s ID,.

Partcipant Name______________

Year of birth_________________

Sex _________M/F

Ask the participant about how they took AL:

- - 1. What time did you take your Coartem last night?

*S: Je ulimeza (dawa ya malaria) coartem saa ngapi jana usiku?*

*L: Ni mwonyo coartem (yadh malaria) saa adi otieno manyoro?*

________________

- - 1. How did you take the drugs?

*S: Ulimezaje hizi madawa?*

*L: Nimwonyo yadhgi nade?*

________________

- - 1. Did you take the drugs with any food/fluids?

*S: Je ulimeaza madawa na chakula au kinyuaji chochote?*

*L: Be nimwonyo yath gi chiemo kata math moramora?*

________________

Then ask the participant the following questions e.g. “In the last 24 hours have you had a Headache?” Write down the answer in the relevant column, like this: put a (**Y**) for “Yes”, a (**N**) for “No” and a “**DK**“ for “Don’t know”. Continue with the next problem and record the answers until all have been asked about. For an adverse event (i.e. where Y is recorded)., document each event on the following adverse reporting form. If any event is termed as severe/life threatening complete the second serious adverse event reporting form as well.

Below are the questions translated into Luo, and Kiswahili.

| **Questions** | | | **(Y/N/DK)** |
| --- | --- | --- | --- |
| **ENGLISH** (In the last 24hrs have you had…….. | **LUO** (Kuom seche piero ariyo gi ang’wen mokalo, be isebdo gi….. | **KISWAHILI** (Kwa masaa ishirini na manne yaliyopita,je umehisi…… |  |
| **1.Headache** | Wich bar | Kuumwa na kichwa |  |
| **2. Itching/or rash** | Guonyruok/guonyo | Kuwashwa ama harara |  |
| **3. Difficulty in breathing** | Pek mar yueyo | Ugumu wa kupumua |  |
| **4.Fatigue/body weakness** | Jony mar del | Uchovu ama unyonge wa mwili |  |
| **5.Dizziness** | Kawirawira | Kusinziasinzia |  |
| **6. Muscular pain** | Rem mar leche | Maumivu ya misuli |  |
| **7. Joint pains** | Rem mar fuonde | Maumivu ya viungo |  |
| **8. Vomiting/nausea** | Ng’ok/chuny lep | Kutapika ama kuchafukwa na moyo |  |
| **9. Fever** | Liet mar del | Joto jingi |  |
| **10. Stomachache** | Ich kach | Kuumwa na tumbo |  |
| **11.Others/specify** | Mamoko/wachi | Mengineyo/fafanua |  |

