# H4: Guidelines for Grading Patient Symptoms, signs and laboratory findings

## Table A. Guidelines for grading patient symptoms

|  | **Grade 1**  **MILD** | **Grade 2**  **MODERATE** | **Grade 3**  **SEVERE** | **Grade 4**  **LIFE THREATENING** |
| --- | --- | --- | --- | --- |
| **Subjective fever in the past 24 h** | N/A | Present (Yes) | N/A | N/A |
| ***Weakness*** | Mild decrease in activity; For children – weak, but still playing | Moderate decrease in activity; For children – weak, and playing limited | Not participating in usual activities; For children – not playing | Prostration |
| **Muscle and/or joint aches*** | Mild and/or localized complaints | Diffuse complaints | Objective weakness; function limited | N/A |
| **Headache*** | Mild, no treatment required | Transient, moderate; treatment required | Severe, constant; requires narcotic therapy | Intractable; requires repeated narcotic therapy |
| **Anorexia** | Decreased appetite, but still taking solid food | Decreased appetite, avoiding solid food but taking liquids | Appetite very decreased; Refusing to breast feed, no solids or liquids taken (< 2 years < 12 hr; > 2 years < 24 hr) | Appetite very decreased; Refusing to breast feed, no solids or liquids taken (< 2 years > 12 hr; > 2 years > 24 hr) |
| **Nausea*** | Mild, transient feeling of impending vomiting; maintains reasonable intake | Moderate and/or constant feeling of impending vomiting; intake decreased | Severe, constant feeling of impending emesis; intake decreased significantly | N/A |
| **Vomiting** | 1 episode per day | 2-3 episodes per day | Orthostatic hypotension or IV fluids required | Hypotensive shock or hospitalisation required for IV fluid therapy |
| **Abdominal pain*** | Mild (1-3 on a scale of 1 to 10) | Moderate (4-6 on a scale of 1 to 10) | Moderate to severe (> 7 on a scale of 1 to 10) | Severe – hospitalilsation for treatment |
| **Diarrhea** | Transient 3-4 loose stools/day | 5-7 loose stools/day | Orthostatic hypotension or > 7 loose stools/day or IV fluids required | Hypotensive shock or hospitalilsation for IV fluid therapy required |
| **Cough** | Transient / intermittent | Persistent / constant | Uncontrolled | Cyanosis, stridor, severe shortness of breath |
| **Pruritis** | Transient pruritis | Pruritis that disturbs sleep | Severe, constant pruritis, sleep disturbed | N/A |

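### Appendix G records any symptom in the last 24 hours as an FSAT adverse event, with no pre-dose symptom record to show whether it is new or worse

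*Protocol*

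**What the plan says.** Appendix G of the Protocol is the side-effect form for FSAT. It starts with the instruction "Call up each participant treated", asks "What time did you take your Coartem last night", and then goes through ten named symptoms and an open item, in the style "In the last 24 hours have you had a Headache". The list includes headache, fever, weakness, muscle and joint pain, and vomiting or nausea. The rule for turning an answer into an event is: "For an adverse event (i.e. where Y is recorded)., document each event on the following adverse reporting form". Each event goes to form H1 in Appendix H.

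On timing, section 9f (intervention phase, FSAT) says: "This monitoring will happen on all days of treatment and one week after the start of treatment". The first dose is supervised. Teams return on the second and third treatment days and note side effects at those visits.

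On what is known before treatment, section 9f says of people aged 6 months to 20 years: "For this age group all individuals will be tested for parasites using RDTs regardless of presence of symptoms or not". Their listed procedures are a rapid test, haemoglobin and blood samples. For the rest, "all other individuals aged above 20 years will have their temperature by ear thermometer", with a rapid test if febrile. No symptom questionnaire is set before the first dose in either group.

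**The concern.** A symptom checklist given only after treatment records what people feel. It does not show what changed. To read a yes as a possible effect of AL, one needs to know whether the person had that complaint before the first tablet. Several listed symptoms are also symptoms of malaria, and section 9f says that FSAT reaches symptomatic as well as asymptomatic carriers, plus household members with no detectable parasites.

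At stake is how far the side-effect record can be interpreted. The Protocol relies on active follow-up of everyone given AL when it explains the safety of treating household members, which section 12c says goes beyond the national strategy. A record that mixes illness already present with drug effects supports that purpose less well. A baseline that was never taken cannot be restored at analysis.

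**Working it through.** The Protocol states no adverse event rate, safety sample size or safety threshold, so there is no figure to reproduce. The check is a comparison of provisions.

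1. **Rule.** Appendix G makes every Y an adverse event. It sets no condition on newness, worsening or onset after the first dose.

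2. **Contrast with the sister form.** Appendix F, for spraying and nets, asks about symptoms since the house was sprayed or the nets were issued. That ties the answer to exposure. Appendix G uses a rolling 24-hour window with no such anchor, although FSAT is the intervention that deliberately includes people who may already be ill.

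3. **Window.** The question about last night's tablets presupposes an earlier dose, so the form is in use from the second treatment day. At that visit 24 hours reaches back to about the first dose. A headache or fever that began before dosing and has persisted is a Y.

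4. **Pre-dose data.**
   - Age 6 months to 20 years: no temperature or symptom list in the FSAT procedures.
   - Over 20 years: temperature only. A person in this group tested because of fever and found positive had fever before the first dose. If it is still reported the next day, it becomes an adverse event.
   - Survey participants: temperature, and fever in the last two weeks and 24 hours (section 9g, Appendix E). This covers a random sample of up to 100 per hotspot and none of the other Appendix G symptoms. Section 11 runs FSAT and the baseline survey at the same time without giving their order within a compound.

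5. **Form H1.** It takes an onset date, maximum severity and a relationship grade from 0 (none) to 4 (definite). It has no first-dose date, no time of onset and no field for presence before dosing. A symptom that began earlier on the day of the first dose looks the same as one that began after it. Maximum severity without a starting severity cannot show worsening. The date the drug was started, and other illness as a cause, appear only on the serious adverse event form.

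6. **Grading.** Table A in Appendix H4 gives "Subjective fever in the past 24 h" one grade only, moderate. A fever carried over is therefore recorded as a Grade 2 event.

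**The case against.** The strongest reply is that recording an event and attributing it are separate steps. Appendix G captures broadly. H1 then asks for onset and relationship, so a headache that began two days before treatment can be dated accordingly and graded 0. The Protocol names no safety endpoint, and the handling of earlier onsets in tables is commonly left to a statistical analysis plan. Many treated people are symptom-free or parasite-free. All of this stands. It limits the point to the symptomatic share and to the quality of the evidence on which attribution rests. It does not answer that point, because onset and relationship depend on recall and judgement with no contemporaneous pre-dose record.

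Some stronger readings are tempting but not supported:

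- **Malaria symptoms are counted as effects of FSAT.** They are recorded as events on a form labelled by intervention, but H1 allows them to be judged unrelated.
- **On the first treatment day the whole window precedes the drug.** Monitoring on all treatment days might suggest this, but the question about last night's tablets and the placing of side-effect notes at the return visits point to use from the second day.
- **Nothing at all is known before dosing.** Temperature in people over 20 and the survey sample's temperature and fever history are partial exceptions.
- **A numerical inflation factor.** If a share b has a persisting symptom and AL newly causes it in a share t, the form records 1 - (1 - b)(1 - t). With t = 5%, b = 0 gives 5%, b = 10% gives 14.5% (2.9 times 5%) and b = 30% gives 33.5%. Neither input is in the documents, and the sum ignores onset and relationship, so no factor can be claimed.

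**Conclusion.** The point holds in limited form. The rule in Appendix G, together with the absence of a pre-dose symptom list, means that persisting complaints will be recorded as FSAT adverse events. Only the recalled onset date and judged relationship on H1 separate them from effects of AL.

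This rests on two assumptions: that some treated people have symptoms before dosing, which section 9f allows by including symptomatic carriers, and that some of those symptoms last to the next-day visit. How many do so is not stated, so the over-count has no calculable size. It could be small if most treated people are symptom-free.

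The effect is confined to the descriptive safety record. Parasite prevalence, serology, the sample size and the planned tests are untouched. This is a worthwhile improvement to the forms and does not threaten the trial's main result.

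**What to change.** Four changes, all to forms and instructions:

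- Complete the Appendix G symptom list once, before the supervised first dose, marked as baseline, with a severity from H1's 1 to 4 scale for each symptom present.
- Replace the Appendix G rule so that an FSAT adverse event is a symptom absent from that record or worse than it. As Table A has a single grade for subjective fever, the comparison for that item is presence or absence.
- Add two fields to H1: present before first dose (Y/N), and date of first dose.
- If events are later split by rapid test result, limit the split to people who had a test. Afebrile people over 20 get no routine rapid test in FSAT and would have no result to classify by.

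The cost is about a minute more per treated person at a visit already planned, plus reprinting and brief training. Reported event counts will be lower than under the present rule, so the report should state the definition used.

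No dose, treatment or referral rule is affected.

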   1. YES
   2. NO, REASON_____________
2. Record Barcode number and date on microcontainer

Barcode Number: ________________________**Appendix F: Side effects monitoring form form insecticides**

Ask the head of house whether anyone in the house has suffered from the following symptoms since we sprayed the house/issued bednets

Area (Cell)_____________

Compound/house code_______________

| **Questions** | | | **Response (Y/N/DK)** |
| --- | --- | --- | --- |
| **ENGLISH** (Since we carried out IRS/gave bednets have you had…….. | **LUO** (Nyaka wa kir yath/chiw nede, be isebdo gi….. | **KISWAHILI** (Tangu tunyunyize dawa/gawa neti, je umehisi…… |  |
| **1.Headache** | Wich bar | Kuumwa na kichwa |  |
| **2. Itching/or rash** | Guonyruok/guonyo | Kuwashwa ama harara |  |
| **3. Difficulty in breathing** | Pek mar yueyo | Ugumu wa kupumua |  |
| **4.Dizziness** | Kawirawira | Kusinziasinzia |  |
| **5. Vomiting/nausea** | Ng’ok/chuny lep | Kutapika ama kuchafukwa na moyo |  |
| **6. Stomachache** | Ich kach | Kuumwa na tumbo |  |
| **7.Others/specify** | Mamoko/wachi | Mengineyo/fafanua |  |

If Y is answered to any of the above ask the head of the house which person/s suffered these symptoms and then call up each participant and complete the adverse reporting form. If serious also complete the serious adverse event form.

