**Appendix H: Adverse event forms**

**H1: Adverse event reporting form**

| ADVERSE EVENT REPORTING FORM | | | | | | | CIRCLE AS APPROPRIATE:FSAT/ IRS/LLIN | | | | | | |
| --- | --- | --- | --- | --- | --- | --- | --- | --- | --- | --- | --- | --- | --- |
| **Person ID:**  ___________ | **Cell:** | | | | **Compound/house code:** | | | | **Date:**  \|___\|___\| / \|___\|___\| / \|___\|___\| | | | | |
|  | ***Complete on day first reported*** | | | | ***Complete on day first reported and update as needed*** | | | | | | | ***Complete on final day*** | |
| **Event** | **Date event onset (d)** | **Date event report (e)** | **Name person reporting** | **Max severity* (f)** | | **Max relationship† (g)** | | **Serious? ‡ *(Y/N)*(h)** | | **Episodic?**  ***(Y/N)*(i)** | **Outcome †† (j)** | | **Date event resolved‡‡ (k)** |
|  |  |  |  |  | |  | |  | |  |  | |  |
|  |  |  |  |  | |  | |  | |  |  | |  |
|  |  |  |  |  | |  | |  | |  |  | |  |
|  |  |  |  |  | |  | |  | |  |  | |  |
|  |  |  |  |  | |  | |  | |  |  | |  |

*** Severity:** Rank on scale of 1-4: mild = 1; moderate = 2; severe = 3, life-threatening = 4 **† Relationship:** Rank on scale of 0-4: none = 0; unlikely = 1; possible = 2; probable = 3; definite = 4

**‡ Serious:** Criteria for SAE: fatal, life-threatening, results in or prolongs hospitalization, results in significant or persistent disability or capacity requires medical / surgical intervention to prevent serious outcome.

If serious, report to core facility staff immediately.

**†† Outcome:** Rank on scale of 1-5: resolved without sequelae = 1; resolved with sequelae = 2; AE still present at study end/discontinuation, but improving = 3; subject died = 4; unknown = 5

**‡‡ Date event resolved:** Complete on Day 42 – If AE still ongoing at end of follow-up, indicate in question.

| SERIOUS adverse event form – initial report | | **Date of SAE Report:**  \|____\|____\|/\|____\|____\|/\|____\|____\|  *day month year* | | | |
| --- | --- | --- | --- | --- | --- |
| **Person ID:**  \|_____\|_____\|_____\|_____\|_____\|_____\|_____\| | | **Date enrolled:**  \|____\|____\|/\|____\|____\|/\|____\|____\|  *day month year* | | | |
| **Person name:** | | **Age:** \|_____\|_____\| years | | **Gender:**  Male Female | |
| **Parent name:** | |  | | | |
| **Event description**:__________________________________________________________________________________________________  *(symptom, sign, or laboratory abnormality)* | | | | | |

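### Appendix G triggers the serious adverse event form by severity grade, while Appendix F, form H1 and the form itself rest on seriousness

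*Protocol*

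**What the plan says.** Four places in the protocol's appendices bear on when the SAE form is completed.

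- **Appendix G** (monitoring after AL treatment). For each symptom answered yes, staff are told to "document each event on the following adverse reporting form", which is form H1. The next sentence adds the SAE form: "If any event is termed as severe/life threatening complete the second serious adverse event reporting form as well".
- **Appendix F** (monitoring after spraying or net distribution). After the adverse event form, the instruction is "If serious also complete the serious adverse event form".
- **Appendix H, form H1** (one form for all three interventions). Severity and seriousness have separate columns. Severity is ranked thus: "Rank on scale of 1-4: mild = 1; moderate = 2; severe = 3, life-threatening = 4". Seriousness is defined by what the event led to: "Criteria for SAE: fatal, life-threatening, results in or prolongs hospitalization, results in significant or persistent disability or capacity requires medical / surgical intervention". H1 adds: "If serious, report to core facility staff immediately".
- **Appendix H, SAE initial report**. The named reasons for calling an event serious match those on H1. Severity is not among them. Maximum severity is asked separately, and mild and moderate are both permitted answers.

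Table A in H4 supplies the grading guidelines for individual symptoms.

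**The concern.** Severity describes how intense an event is; seriousness describes what it led to. The protocol keeps the two apart on H1 and on the SAE form, then uses severity as the trigger in Appendix G and seriousness as the trigger in Appendix F. Field staff who follow Appendix G literally will complete the SAE form for a different set of events from the one that the form was built to record.

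What is at stake is detail on individual cases. Of the forms shown, only the SAE forms collect a narrative of the event, the AL dosing schedule at onset, the dates of first and last dose, and possible alternative causes. That information is most wanted for a hospitalisation after AL. It matters here because section 9f has AL given to house members who may have no detectable parasites, and section 12c undertakes to monitor and document side effects of all the interventions closely.

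**Working it through.** No arithmetic applies to the contradiction itself. The check sets the two triggers side by side and runs example events through both, using Table A for the grade and the H1 criteria for seriousness.

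**Reading used.** The Appendix G trigger is taken to mean severe or life-threatening, that is, 3 or 4 on the H1 severity scale.

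| Event after AL | Grade (Table A) | Serious on H1? | Appendix G directs it to the SAE form? |
|---|---|---|---|
| Fever leading to hospitalisation, graded on the fever row | 2 (the only grade offered) | Yes | No |
| Severe, constant pruritus with no further consequence | 3 | No | Yes |
| Vomiting or diarrhoea with hospitalisation for intravenous fluids | 4 | Yes | Yes |
| Abdominal pain or behavioural change with hospitalisation | 4 | Yes | Yes |
| Any life-threatening event | 4 | Yes | Yes |

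**Line 1: serious but not directed to the form.** The row "Subjective fever in the past 24 h" has an entry only under Grade 2; Grades 1, 3 and 4 are marked not applicable. Fever is item 9 on the Appendix G checklist, so the case falls within the questions staff must ask. The event still goes onto H1, is marked serious there, and must be reported to core staff immediately. What Appendix G lacks is an instruction to complete the SAE form.

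**Line 2: directed to the form but not serious.** Itching is item 2 on the same checklist. Grade 3 pruritus requires only that the symptom be severe and constant and disturb sleep, which meets none of the H1 criteria. Appendix G nevertheless calls for the SAE form.

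**Lines 3 to 5: agreement.** In four rows of Table A (vomiting, diarrhoea, abdominal pain, behavioural change) the Grade 4 wording itself names hospitalisation. An admission for one of these is Grade 4 and meets both triggers.

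**Where the grade cannot reach the trigger.** Table A has 16 symptom rows. Two of them, subjective fever and viral upper respiratory infection, have no Grade 3 or 4, so an event graded only on either row cannot meet the Appendix G trigger. The other 16 − 2 = 14 define a Grade 3.

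**Cross-check against the SAE form.** The form permits mild or moderate as maximum severity, so it expects serious events of low grade. Read literally, Appendix G never sends staff to the form for such events.

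**The case against.** The strongest reply is that nothing serious is lost. Appendix G sends every event to H1, whose seriousness column is outcome-based and whose instruction for immediate reporting does not depend on grade. The Appendix G sentence adds a step and does not say that the SAE form is used only for severe events. Core staff, once alerted, could complete the form. Table A is headed as guidelines, and a febrile patient ill enough for admission might also be graded on weakness or convulsion. A severe but non-serious event sent to the SAE form would be recognisable, because none of the named reasons would fit.

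Most of this stands, and it limits the point. It does not remove the conflict: no sentence in Appendix G tells staff to complete the SAE form for a serious event of low grade, H1 names only the report to core staff, and Appendix F shows that a seriousness trigger was available.

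Three stronger readings are tempting and are not supported.

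- *A hospitalised participant with a moderate event goes unreported.* H1 requires the event to be marked serious and reported immediately. Only the direction to the SAE form is missing.
- *Serious events after AL and after insecticides cannot be compared.* H1 is common to all three interventions and has one seriousness definition, so counts can be taken from that column under one rule. The stated objectives, outcomes and analysis include no such comparison.
- *Most Grade 3 entries would generate a non-serious SAE form.* The 14 rows can be counted, but how many of them imply an H1 criterion is a matter of judgement. Headache needing narcotics, a seizure, or aches that limit function could each be argued either way, and rows say nothing about frequency.

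Dizziness and difficulty in breathing have no row of their own in Table A. That is missing detail in a guideline table, partly covered by the Grade 4 cough entry and by H1's general scale, and is not part of this point.

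**Conclusion.** The inconsistency is real and is wrong as written. Appendix G keys the SAE form to severity; Appendix F, the H1 criteria and the form's own reasons key it to seriousness. In AL-treated people, a serious event graded mild or moderate is marked serious and escalated through H1 but is not directed to the SAE form, while a severe event that meets no seriousness criterion is.

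The size is modest. For four symptoms, hospitalisation itself sets Grade 4 and closes the gap, and H1 acts as a backstop for the rest. The documents give no event rates, so the number of affected forms cannot be estimated. The primary outcome, power and analysis are unaffected. The conclusion assumes that staff follow Appendix G as worded, read its trigger as Grade 3 or 4, and grade the event on its own row of Table A.

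**What to change.** Reconcile the passages. Replace the trigger sentence in Appendix G, and align the one in Appendix F, so that both say the same thing: the SAE form is completed for any event that meets an H1 seriousness criterion, whatever its severity grade, and severity is recorded separately in its own column. It would help to repeat that sentence beside the H1 instruction to report to core staff, so that the report and the form are linked.

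The cost is a change of wording on the forms and a short briefing for field staff. No visits, samples or analyses are added. The likely effect is fewer SAE forms for non-serious symptoms and a complete form for each event marked serious on H1.
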